### Statistical methods

#### Sample size determination

The sample size calculation for this RCT was based on success quit rates from previous smoking cessation studies [21, 33, 34]. We computed that 174 subjects (87 per each study arm) will be required to have 90% power with two-sided 0.05 significance level test to detect a difference of at least 18.7% between treatment groups for CAR 9–24 weeks. Allowing for a conservative attrition rate of approximately 40%, the target number of participants will be increased to a total of 300 (150 per each study arm).

#### Methods of analyses

Baseline and demographic data will be listed for all treatment groups. Summary statistics will be provided for each treatment group. At baseline, differences between varenicline and placebo groups will be evaluated by means of one-way analysis of variance and Mann–Whitney *U*-test for normally and not normally distributed continuous variables, respectively; *χ*^2^ test will be used for categorical variables. The secondary endpoints will be analyzed using procedures similar to that described above for the primary endpoint. Intention-to-treat analysis will be adopted for efficacy evaluation, assuming that subjects lost to follow-up continued smoking.

Safety data will be summarized for both treatment groups and summary statistics provided.

Any events documented in the period from the point of treatment initiation until 1 week after randomized treatment has been discontinued (V14) will be considered as relevant to the safety analysis. AEs will be coded using MedDRA (Medical Dictionary for Regulatory Activities) and assigned grades based on NCI CTCAE (National Cancer Institute Common Terminology Criteria for Adverse Events). Between-groups comparisons for both individual and clustered AE rates will be carried out using χ^2^ testing or Fisher’s exact test, as appropriate.

Multiple logistic regression models will be built to identify independent predictors associated with CARs at week 12, week 24, and week 52.

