#### Safety end points

A summary table will present the number of events (includes lab data), number of subjects and severity of adverse events (AEs), and serious adverse events (SAEs). Any events documented in the period from the point of treatment initiation until 1 week after randomized treatment has been discontinued (V14) will be considered as relevant to the analysis.

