### Study visits

The study will consist of a total of 19 visits: a screening visit, a baseline visit (V1), 12 study visits during the 12-week treatment phase (V2 to V13, of which 4 will be telephone contact visits) followed by an additional 5 study visits during the 40-week follow-up phase (V14 to V18, of which 2 will be telephone contact visits) (Fig. 1). Activities carried out during study visits are detailed in Table 1.

**Table 1 Tab1:** Study schedule/flowchart

**Procedure**	Sc V0	BL V1	Wk 1 V2	Wk 2 V3	Wk 3 V4	Wk 4 V5	Wk 5 TC V6	Wk 6 V7	Wk 7 TC V8	Wk 8 V9	Wk 9 TC V10	Wk 10 V11	Wk 11 TC V12	Wk 12 V13	Wk 13 V14	Wk 24 V15	Wk 36 TC V16	Wk 44 TC V17	Wk 52 V18
Informed consent		X																	
Eligibility Criteria	X	X																	
Medical Hx	X	X																	
Antidiabetic drug use		X	X	X	X	X		X		X		X		X	X	X			X
Smoking Hx	X	X																	
Cigarette consumption	X	X	X	X	X	X	X	X	X	X	X	X	X	X	X	X	X	X	X
Exhaled CO		X	X	X	X	X		X		X		X		X	X	X			X
BP, HR	X	X	X	X	X	X		X		X		X		X	X	X			X
BMI, waist		X												X		X			X
Sociodemographics		X																	
Motivation to quit by VAS		X																	
FTCD		X																	
BDI & BAI		X																	
Self-Efficacy to quit by VAS		X																	
Cessation counseling		X	X	X	X	X	X	X	X	X	X	X	X	X	X	X	X	X	X
Adverse events		X	X	X	X	X		X		X		X		X					
Blood chemistry and CBC	X	X		X											X				
Urinalysis	X	X		X											X				
DM lab tests		X													X	X			X
Dispense study drug*		X	X	X	X	X		X		X		X							
Dosing record			X	X	X	X		X		X		X		X					

*Sc* screening, *BL* baseline, *TC* telephone contact, *CO* carbon monoxide, *HR* heart rate, *BP* blood pressure, *BMI* body mass index, *VAS* visual analog score, *FTCD* Fagerstrom Test for Cigarette Dependence, *BDI* beck depression inventory, *BAI* beck anxiety inventory, *QoL* quality of life, *CBC* complete blood count, *DM* diabetes mellitus

*Dispense study drug – a week supply of drug/placebo is dispensed at each visit with the exception of Wk 4, Wk 6, Wk 8 and Wk 10 when a whole 2 weeks supply is given

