#### Baseline visit (V1)

The Baseline Visit will be scheduled no less than 3 working days after screening so that laboratory results would be available for review. Patients with abnormal laboratory results judged to be clinically significant will not be considered for inclusion. Eligible patients are asked to go over the patient information sheet and to sign the consent form. General socio-demographic features, medical hx, drug prescriptions, smoking hx, and motivation to quit will be noted in the chronic renal failure (CRF). The following baseline assessments will be carried out: number of cigarette smoked/day, eCO levels, blood pressure, HR, BMI, waist circumference, and questionnaires (Fagerström Test for Cigarette Dependence (FTCD), Beck Depression Inventory (BDI), Beck Anxiety Inventory (BAI)). Blood and urine samples will be collected for standard clinical laboratory evaluations (including fasting blood glucose, HbA1C, insulinemia, and albumin to creatinine ratio). Any AEs will be noted in the CRF. Eligibility criteria will be reviewed again prior to randomization. Regardless of their assignment, all patients will receive smoking cessation counseling and instructed to set a TQD 1–3 days before the next study visit (visit 2 at Week 1). Patients will receive a full week supply of their assigned treatment prior to check-out (either varenicline or placebo depending on the study-arm allocation). Study drug will be dispensed according to the plan illustrated in Table1.

#### Treatment study visits 2 to 13

After V1, patients will return for their treatment phase visits (V2–V13). With the exclusion of Visits 6, 8, 10 and 12 (telephone contact visits), patients will return to attend weekly visits to the clinic over the following 12 weeks. Study visits will occur within 3 days of each scheduled visit date. Patients returning for their Week-1 visit (i.e. V2; TQD-visit) must have adhered to their TQD, abstaining from smoking for 1–3 days before the study visit. At each visit, patients will be reminded of the importance of staying cigarette free and will receive professional counseling for relapse prevention. Number of cigarette smoked/day, eCO levels, blood pressure, HR (BMI, and waist circumference only at Week-12 visit), and AEs will be noted in the CRF. Any unused study drug will be returned to the principal investigator. Patients will receive a supply of their assigned treatment prior to check-out according to the plan illustrated in Table1.

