#### Follow-up study visits 14 to 18

Following completion of the treatment phase (V2–V13), patients will continue in the nontreatment follow-up phase of study. Only patients completing the week-12 visit will be eligible to continue in the nontreatment follow-up phase (V14–V18). With the exclusion of Visits 16 and 17 (telephone contact visits), patients will return for their study visits at week-13 (V14), week-24 (V15), and week-52 (V18). Number of cigarette smoked/day, eCO levels, BP and HR (BMI, and waist circumference only at week-24 and week-52 visits) will be noted in the CRF. Blood and urine samples will be collected for evaluation of fasting blood glucose, HbA1C, insulinemia, and albumin to creatinine ratio at week-24 and week-52 visits.

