### Safety reporting

#### Adverse events

All observed or volunteered AEs, regardless of treatment group or suspected causal relationship to study drug, will be recorded. This includes symptoms thought to be related to withdrawal from nicotine. Events involving adverse drug reactions, illnesses with onset during the study, or exacerbations of pre-existing illnesses should be recorded. Exacerbation of the disease under study (type 2 diabetes), is defined as a manifestation (sign or symptom) of the illness that indicates a significant increase in the severity of the illness as compared to the severity noted at the start of the trial. It may include worsening or increase in severity of signs or symptoms of the illness, increase in frequency of signs and symptoms of an intermittent illness, or the appearance of a new manifestation/complication. Exacerbation of a pre-existing illness should be considered when a subject requires new or additional concomitant therapy for the treatment of that illness during the trial. In addition, clinically significant changes in physical examination findings and abnormal objective test findings (e.g., laboratory) should also be recorded as AEs. For all AEs, the investigator must pursue and obtain information adequate both to determine the outcome of the AE and to assess whether it meets the criteria for classification as a SAE. For all AEs, sufficient information should be obtained by the investigator to determine the causality of the AEs (i.e., study drug or other illness).

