#### Serious adverse events

All SAEs (as defined below) regardless of treatment group or suspected relationship to study drug must be reported immediately. A SAE is any adverse drug experience occurring at any dose that:

1. Results in death;

2. Is life-threatening;

3. Results in inpatient hospitalization or prolongation of existing hospitalization;

4. Results in a persistent or significant disability/incapacity.

Any SAE or death must be reported immediately independent of the circumstances or suspected cause if it occurs or comes to the attention of the investigator at any time during the study through 30 days after the last administration of study drug. Any SAE occurring beyond 30 days after the last administration of study drug must be promptly reported if a causal relationship to study drug is suspected.

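### The adverse event window closes at V14 (week 13), but Table 1 schedules the last adverse event entry at V13 (week 12)

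*Protocol article*

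**What the plan says.** The safety window is stated twice and ends at the same place each time. Safety end points includes events "until 1 week after randomized treatment has been discontinued (V14) will be considered as relevant to the analysis", and Methods of analyses repeats this for the safety analysis: "until 1 week after randomized treatment has been discontinued (V14) will be considered as relevant to the safety analysis". Both name V14, which Table 1 and the section Follow-up study visits 14 to 18 place at week 13 as a clinic visit. Methods of analyses then compares adverse event rates between the arms by chi-square or Fisher's exact test.

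The section Study visits hands the schedule to the table: "Activities carried out during study visits are detailed in Table 1". The adverse event row of Table 1 is marked at V1, V2, V3, V4, V5, V7, V9, V11 and V13, and is blank from V14 onwards.

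The visit descriptions follow the same pattern. For V2 to V13 the list of recorded items ends "HR (BMI, and waist circumference only at Week-12 visit), and AEs will be noted in the CRF". For V14 to V18 the corresponding list runs to "eCO levels, BP and HR (BMI, and waist circumference only at week-24 and week-52 visits) will be noted in the CRF", and adverse events are not in it.

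Two general rules apply besides the schedule. The Adverse events section states that "All observed or volunteered AEs, regardless of treatment group or suspected causal relationship to study drug, will be recorded". The Serious adverse events section requires a report of any serious event that occurs or becomes known "at any time during the study through 30 days after the last administration of study drug".

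**The concern.** An analysis window and the collection schedule behind it should end at the same point. Here the window runs one visit further than the schedule. The extra week is the first week off drug, when symptoms that follow stopping treatment would appear. Counting events in that week is sensible, but only if there is a planned occasion to write them down. The patient attends the clinic at V14, yet adverse events are not among the procedures marked for that visit.

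Safety is a stated aim of the trial. At stake is whether the adverse event rates set against each other really cover the period they are said to cover, and whether a reader can tell which part of that period had scheduled recording behind it.

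**Working it through.** **1. Is the blank cell real?** Table 1 has 19 visit columns, V0 to V18. Split into cells, the adverse event row has exactly 19, with the last mark at week 12, V13. The exhaled CO row and the blood chemistry and blood count row also have 19 cells, and both carry a mark at week 13, V14. The columns are therefore aligned, and the blank is not a product of the text extraction.

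**2. Could an entry have been made at V14?** Eight rows are marked there: antidiabetic drug use, cigarette consumption, exhaled CO, blood pressure and heart rate, cessation counseling, blood chemistry and blood count, urinalysis, and diabetes laboratory tests. The patient is in the clinic.

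**3. Coverage by clinic visit.** The post-baseline clinic visits up to the end of the window are V2, V3, V4, V5, V7, V9, V11, V13 and V14, which makes 9. Adverse events are marked at 8 of them. V14 is the only one without the mark.

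**4. Length of the uncovered stretch, for patients who take the drug for 12 weeks.**
- Treatment lasts 12 weeks: 12 × 7 = 84 days, ending at V13.
- The window ends one week later: 13 × 7 = 91 days, at V14.
- Remainder after the last scheduled entry: 91 − 84 = 7 days, and 7 / 91 = 7.7% of the window.

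These are nominal visit dates.

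**5. Patients who stop early.** The window closes one week after the drug is stopped. A patient who stops by day 84 − 7 = 77 and attends V13 has the whole window behind a visit that carries an adverse event entry. The figure in step 4 does not apply to such a patient.

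**6. What other rules cover in that week.**

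| Type of event, week 12 to week 13 | Covered by |
|---|---|
| Serious | Serious adverse events section, to 30 days after the last dose |
| Laboratory abnormality | V14 blood and urine tests in Table 1, with the criteria in the section on clinical laboratory parameters |
| Non-serious, non-laboratory | General rule in the Adverse events section only; no scheduled entry |

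The third row is what remains. The article gives no event rates, so the number of events in that row cannot be derived.

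**The case against.** The strongest reply is that nothing is contradicted. The window sentences are an inclusion rule for events already documented; they do not promise an entry at the closing visit. V14 is also a natural cut-off, because the end-of-treatment laboratory tests are done there and the summary of events includes laboratory data. The general recording rule has no cut-off at V13, so an event seen or mentioned at V14 must still be recorded. This stands as far as it goes: the week is not unobserved. It does not explain why adverse events have their own row at nine visits and not at the one visit that defines the end of the window.

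A second reply concerns the visit text. The description of V14 to V18 is not a full list. Of the eight procedures that Table 1 marks at V14, it does not give five for that visit: antidiabetic drug use, counseling, blood chemistry and blood count, urinalysis, and diabetes laboratory tests, the last of which it places at weeks 24 and 52 only. Its silence on adverse events is weak support, and the point rests on Table 1.

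A reader might also infer that patients were actively questioned up to week 12 and left to volunteer events afterwards. The article does not support this contrast. Observed or volunteered is the only method of ascertainment it states, and that holds for the whole study. For V2 to V13 it says only that events are noted in the case report form. The difference at V14 is the absence of a scheduled entry, not a documented change of method.

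**Conclusion.** The point holds and is minor. The stated window ends at V14 and the scheduled adverse event entries end at V13. For patients who complete 12 weeks of drug, non-serious, non-laboratory events in the first week off drug have no scheduled entry and rely on the general recording rule. The stretch is nominally 7 of 91 days.

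A reader might take 7.7% as the share of events missed, or take the safety comparison to be biased. Neither follows. The figure is a share of time in one group of patients, and it says nothing about how events are spread over the window. Both arms follow the same schedule, so the documents give no ground for a bias between them. What is affected is the completeness of capture in the last week and the accuracy of its description.

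The conclusion assumes that Table 1 shows the schedule that was followed. The article cannot show whether adverse events were in practice recorded at V14.

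**What to change.** As a matter of design, mark adverse events at V14 in Table 1 and add them to the list for that visit in Follow-up study visits 14 to 18. The cost is a slightly longer existing visit and a few more minor events to code.

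The Results section says that conduct is complete and that data cleaning and analyses are ongoing, so the remedy depends on what was done:

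- **If adverse events were recorded at V14:** correct Table 1 and the follow-up visit text to say so, and keep the window as stated.
- **If they were not:** report adverse event rates to V13 as the scheduled-collection window. Describe week-13 events separately, as observed or volunteered reports, serious adverse events and laboratory findings.

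Either route costs a few lines of text. The second also needs one separate summary of week-13 events. The between-arm test methods stay as planned.

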### Safety reporting

#### Adverse events

All observed or volunteered AEs, regardless of treatment group or suspected causal relationship to study drug, will be recorded. This includes symptoms thought to be related to withdrawal from nicotine. Events involving adverse drug reactions, illnesses with onset during the study, or exacerbations of pre-existing illnesses should be recorded. Exacerbation of the disease under study (type 2 diabetes), is defined as a manifestation (sign or symptom) of the illness that indicates a significant increase in the severity of the illness as compared to the severity noted at the start of the trial. It may include worsening or increase in severity of signs or symptoms of the illness, increase in frequency of signs and symptoms of an intermittent illness, or the appearance of a new manifestation/complication. Exacerbation of a pre-existing illness should be considered when a subject requires new or additional concomitant therapy for the treatment of that illness during the trial. In addition, clinically significant changes in physical examination findings and abnormal objective test findings (e.g., laboratory) should also be recorded as AEs. For all AEs, the investigator must pursue and obtain information adequate both to determine the outcome of the AE and to assess whether it meets the criteria for classification as a SAE. For all AEs, sufficient information should be obtained by the investigator to determine the causality of the AEs (i.e., study drug or other illness).

#### Serious adverse events

All SAEs (as defined below) regardless of treatment group or suspected relationship to study drug must be reported immediately. A SAE is any adverse drug experience occurring at any dose that:

1. Results in death;

2. Is life-threatening;

3. Results in inpatient hospitalization or prolongation of existing hospitalization;

4. Results in a persistent or significant disability/incapacity.

Any SAE or death must be reported immediately independent of the circumstances or suspected cause if it occurs or comes to the attention of the investigator at any time during the study through 30 days after the last administration of study drug. Any SAE occurring beyond 30 days after the last administration of study drug must be promptly reported if a causal relationship to study drug is suspected.

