#### Inclusion criteria

Type 2 diabetic patients (≤ 75 years of age, but > 18 years of age) who met the ADA diagnostic criteria [24]T2DM had been diagnosed for > 12 monthsWith 7.0% ≤ HbA1c ≤ 12.0%Regularly smoking ≥ 10 cigs/day during the past year (with no period of abstinence greater than three months in the past year)Willing to quit. This will be verified by the answer ‘‘YES’’ to both questions ‘‘Do you intend to quit in the next 30 days?’’ and ‘‘Are you interested in taking part in a smoking cessation program?’’Females of nonchildbearing potential (surgically sterilized or at least 2 years postmenopausal) who are not nursing may be included. Females of childbearing potential may be included provided that they are not pregnant, not nursing, and are practicing effective contraception.Subjects must be able to be outpatients and be assessed in a clinic setting.Participating subjects must be able to provide written informed consent.

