#### Exclusion criteria

Subjects currently or within the past 12 months requiring treatment for depression. Subjects with a past or present history of panic disorder, psychosis, or bipolar disorder.Subjects with a current or recent (within the past 12 months) history of alcoholism.Subjects with a requirement to use other medications during the study that might interfere with the evaluation of the study drug (e.g., nicotine replacement therapy).Subjects with a body mass index (BMI) less than 18.5 or greater than 35.Subjects with evidence or history of clinically significant allergic (except for seasonal allergies at time of dosing), endocrine, gastrointestinal, hematological, hepatic, neurologic, pulmonary, or renal disease or a history of cancer (excluding treated basal cell carcinoma and squamous cell carcinoma). Exceptions to this exclusion may include subjects with a history of mild COPD, and stable thyroid disease.Subjects with a history of clinically significant cardiovascular disease. In addition, subjects with uncontrolled hypertension or a screening or baseline systolic blood pressure greater than 160 mm Hg or a diastolic blood pressure greater than 95 mm Hg will be excluded.

The study adheres to the ethical principles of the Declaration of Helsinki and to the International Conference on Harmonization Good Clinical Practice guidelines. The study has been reviewed and approved by the Ethical Review Board of the leading site at the Azienda Ospedaliero Universitaria “Policlinico-V. Emanuele”, Università di Catania, Italy (approval reference number: 009711) and participants will give written informed consent prior to participation in the study. The study has been registered in ClinicalTrial.gov with Trial registration ID: NCT01387425 (https://clinicaltrials.gov/ct2/show/NCT01387425).

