#### Clinical laboratory parameters and abnormal laboratory test results

The results of all laboratory tests required by the protocol will be recorded. All clinically important abnormal laboratory tests occurring during the study will be repeated at appropriate intervals until they return either to baseline or to a level deemed acceptable by the investigator or until a diagnosis that explains them is made. The criteria for determining whether an abnormal laboratory test result should be reported as an AE are as follows:

1. Test result is associated with accompanying symptoms, and/or.

2. Test result requires additional diagnostic testing or medical/surgical intervention, and/or.

3. Test result leads to a change in study dosing or discontinuation from the study, significant.

additional concomitant drug treatment or other therapy, and/or.

4. Test result leads to any of the outcomes included in the definition of a SAE, and/or 5. Test result is considered to be an AE by the investigator.

The following tests will be completed at the screening and baseline visits: blood chemistry (including sodium, potassium, chloride, BUN, creatinine, glucose, SGOT, SGPT, LDH, alkaline phosphatase, total bilirubin, cholesterol, and triglycerides) and complete blood count. In the event of clinically significant abnormalities, urine samples will be sent for urinalysis. Moreover, the following additional lab tests will be carried out at screening, baseline, week 13, week 24 and week 52 (HbA1c, fasting glucose, total cholesterol, HDL, LDL, triglycerides, insulinemia, albumin to creatinine ratio, and plasma creatinine).

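### The SAE definition is a closed list of four outcomes, so a medically important event that meets none of them is not classed, escalated or counted as serious

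*Protocol article*

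**What the plan says.** All statements are in the protocol article.

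- **Serious adverse events.** SAEs must be reported at once, and the text points to the definition that follows: "A SAE is any adverse drug experience occurring at any dose that", then four numbered items: "Results in death"; "Is life-threatening"; "Results in inpatient hospitalization or prolongation of existing hospitalization"; "Results in a persistent or significant disability/incapacity". The list ends there. The section says twice that reporting does not depend on the suspected cause.
- **Adverse events.** Every AE is recorded whatever its suspected cause, and the investigator judges each one against the SAE criteria.
- **Safety end points.** AEs and SAEs are tabulated. Events count from the start of treatment until one week after its end (V14).
- **Inclusion criteria.** "Females of childbearing potential may be included provided that they are not pregnant, not nursing, and are practicing effective contraception".
- **Ethics paragraph at the end of Exclusion criteria.** "The study adheres to the ethical principles of the Declaration of Helsinki and to the International Conference on Harmonization Good Clinical Practice guidelines".
- **Results.** 300 participants have been randomized and conduct is complete. Data cleaning and analysis are still under way.

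**The concern.** The definition sets three things: which events must be reported immediately, how each AE is classified, and what enters the SAE summary. Because the list is closed, an investigator has no basis in it for calling an event serious on medical judgement. A seizure or a serious glycaemic event managed without admission, and neither life-threatening nor disabling, is non-serious under this rule. In a trial of people with diabetes whose stated aims include safety, such events are ones a reader would expect to find among the SAEs.

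The trial also admits women of childbearing potential on condition of contraception, so it treats exposure in pregnancy as a risk. The definition has no criterion under which a birth defect after exposure would be serious in its own right.

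A wording problem adds to this. The duty to report disregards suspected causality, but the definition is phrased in terms of an experience of the drug.

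**Working it through.** No arithmetic applies. The check is a count of criteria and a comparison of sections.

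**1. Count the criteria.** Death, threat to life, hospitalization or its prolongation, disability or incapacity: 4. Mentions of congenital anomaly or birth defect anywhere in the article: 0. Mentions of a medically important event criterion: 0. Pregnancy appears only in the eligibility criteria.

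**2. Is the list open or closed?** Nothing in it marks the items as examples, and there is no item for investigator judgement. The section on laboratory results differs: its last criterion lets the investigator call a result an AE on judgement alone. The authors used a catch-all there and not here.

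**3. Is this just condensation in a journal article?** The article neither defers nor summarises the definition. It refers the reader to it and writes it out as the working rule. The point is therefore a rule stated too narrowly, not a detail left to the full protocol.

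**4. Follow an event that meets none of the four outcomes.**

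| Step | Section | Result |
|---|---|---|
| Recorded as an AE | Adverse events | Yes |
| Coded and graded for severity | Methods of analyses | Yes |
| Compared between arms as an AE | Methods of analyses | Yes |
| Classed as an SAE | Adverse events; Serious adverse events | No |
| Reported immediately as an SAE | Serious adverse events | No |
| Counted among SAEs | Safety end points | No |

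The event stays in the data. Only the last three steps are lost. A CTCAE grade does not restore them, because it measures severity and the SAE list measures seriousness by outcome.

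**5. Follow a birth defect.** Participants must not be pregnant at entry, and the safety window closes at V14, which is week 13. A pregnancy conceived on treatment cannot reach term by then, so the criterion would hardly change the SAE table. Reporting of the individual case is different. Beyond 30 days after the last dose, the duty covers an SAE with suspected causality. A birth defect is an SAE here only if it happens to meet one of the four outcomes.

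**6. Set the lead-in beside the reporting duty.** The lead-in is specific to the drug; the surrounding sentences require reporting whatever the suspected cause. The two should be reconciled.

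**The case against.** The strongest reply is that little is lost. Every AE is recorded, coded, graded and compared between arms, and the formal comparison named in Methods of analyses is of AE rates, not of SAEs specifically. Any event that threatens life, leads to admission or disables is already an SAE. This stands, and it confines the gap to events that meet none of the four outcomes.

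It can also be said that the list contradicts no other sentence of the article, and that the conflict with ICH-GCP depends on a text that is not in the documents. That is fair. The article shows only the commitment and the four-item list; what the guideline contains is general professional knowledge. The finding therefore rests on what the closed list does within this trial, not on a tally against the guideline.

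Four stronger readings are tempting, and the documents do not support them:

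- **Sites would screen SAEs for causality before reporting.** The section twice instructs otherwise, and those instructions outweigh the loose lead-in. Only a wording correction remains.
- **The narrow list decides when a laboratory result becomes an AE.** One laboratory criterion does refer back to it ("Test result leads to any of the outcomes included in the definition of a SAE"). The five criteria are alternatives, however, and those on symptoms, further testing or intervention, changed treatment and investigator judgement would catch most such results.
- **Table 1 and the test lists show no pregnancy test, so non-pregnancy is not verified.** An article commonly leaves the method of verification to the full protocol. Its absence here is no finding.
- **The SAE count is too low by some percentage.** The article gives no SAE rate and no number of events that would be reclassified. Any percentage would be arithmetic on guesses.

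**Conclusion.** The point holds in a limited form. The SAE definition as printed is closed at four outcomes and omits medically important events and congenital anomaly. Medically important events that meet none of the four are kept as graded AEs but lose SAE status, immediate reporting and a place in the SAE count. The birth-defect omission concerns individual reporting and hardly touches the table.

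The size is unknown. The number of reclassified events could be zero, and only the AE listing can show it. The efficacy analyses are not affected.

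The conclusion assumes that the printed definition is the one the sites used. The full protocol is not shown. If it contains a wider definition, the article misstates it and the text alone needs correcting.

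**What to change.** 1. In Serious adverse events, add two criteria: congenital anomaly or birth defect, and other medically important events as judged by the investigator.
2. Replace the drug-specific lead-in with wording that covers any untoward medical event, whether or not it is thought to be related to the drug, so that it agrees with the reporting duty around it.
3. Conduct is complete, so immediate reporting cannot be put right retrospectively. Before the SAE table is finalised, re-screen the recorded AEs of both arms, blinded to allocation, against the full definition. Report how many events were reclassified in each arm, including none.
4. If the re-screen is not done, state in the report that the SAE counts rest on four criteria and exclude other medically important events.

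The cost is a short text change and one pass through the AE listing. A few events may be relabelled as serious. Doing this blinded and before the table is final keeps the relabelling from being driven by treatment arm.
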